### Data Analysis

#### Phase 1

A systematic review will be conducted using Review Manager (version 5.4; The Cochrane Collaboration). Risk of bias will be assessed according to the revised Cochrane risk-of-bias tool for randomized trials [37]. The Grading of Recommendations Assessment, Development, and Evaluation system will be used to estimate the certainty of the evidence.

#### Phase 2

Data analysis and data collection will take place simultaneously. Theoretical saturation will be determined to terminate the interviews when the information from the last interview has been analyzed and no new themes and ideas have been found. The transcribed texts will be read repeatedly for familiarization and line-by-line coding. Initial codes will generate potential themes. The interview transcripts will be analyzed using thematic analysis, which is an inductive method for identifying, analyzing, and reporting patterns within the data [38]. The NVivo qualitative analysis software will be used to facilitate and manage the analysis. After analyzing and processing the interview transcripts, we will provide a subset of participants with the research findings or interpretations to verify whether they accurately reflect the intended meanings of the participants.

#### Phase 3

The analysis will commence using descriptive statistics, summarizing sociodemographic and clinical characteristics as means and SDs for continuous variables and as frequencies and proportions for categorical variables. The core analysis of the DCE data will used a mixed logit model. This model assesses how the different attributes and levels influence patient choices, with the choice outcome as the dependent variable and the attribute levels as independent variables. The model estimates a regression coefficient (β) for each attribute, where a significant β denotes a meaningful impact on preference, with its sign and magnitude indicating the direction and relative strength of influence, respectively. The associated SD of β quantifies the heterogeneity in preferences for that attribute among participants. All analyses will be conducted using Stata (version 16.0; StataCorp).

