**Objective:**

This study aims to investigate the preferences for traditional Chinese medicine of patients with COPD, the clinical outcomes they are concerned about, and the trade-offs involved in evaluating the factors that influence treatment selection, such as clinical effectiveness, cost, and adverse effects.

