The results of a pilot study conducted by our team suggest that the preference of patients with COPD for TCM may be influenced by factors such as clinical efficacy, side effects, and cost [29]. The findings need to be validated in larger samples. In addition, patient perceptions with regard to specific interventions have not been investigated. In this study, we focus on exploring the preferences of patients with COPD during clinical decision-making. *Preference* is defined as patients’ perceptions of TCM for the treatment of COPD, their appraisal of factors for treatment scenarios, and the balance of harms and benefits within or between interventions.

The discrete choice experiment (DCE) is a stated-preference method originating from Lancaster’s economic theory of value and McFadden’s random utility theory, and it has since been widely applied in health care research [30,31]. DCEs can integrate measures of multiple attributes to obtain results closer to real choices, which can adequately predict actual consumer behavior, being generally used in health care preference surveys today [32,33]. There are currently no studies that have used DCE to investigate the preferences of patients with COPD for TCM. Therefore, we will use mixed methods, including both qualitative and quantitative (DCE) methods to obtain more comprehensive information. We hypothesize that clinical practice will be improved by incorporating patients’ preferences. Our objective is to investigate patients’ preferences for TCM for the treatment of COPD; the clinical outcomes they are concerned about; and the trade-offs for the factors of treatment scenario options, such as clinical effectiveness, cost, and side effects. The main research questions are as follows:

What is patients’ perception (such as effect, side effects, and treatment duration) of TCM for COPD?Which clinical outcomes are of most concern for patients, and which factors are important for treatment scenario options?Which factors will influence patients’ options in terms of the available evidence for specific therapies (eg, efficacy, safety, or economic factors)?

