## Methods

### Study Design

An exploratory, sequential mixed methods study will be conducted involving a qualitative and quantitative study (DCE) [34]. In an exploratory sequential design, data are first collected and analyzed through qualitative investigation, followed by further exploration of themes derived from the qualitative data via a quantitative investigation. The results from both sets of data are then integrated and interpreted [35]. The attributes of the DCE will be identified from a literature review and the qualitative survey based on previous pilot study results [29]. The results of the qualitative and quantitative study phases will be compared to determine the degree of consistency. This study, which is expected to be completed within 1 year, will be divided into three phases, which are illustrated in the procedural diagram (Figure 1): (1) an update of the existing evidence [23] on the efficacy, safety, economic benefits, and patient satisfaction related to TCM in treating COPD (phase 1; 3 months); (2) a qualitative investigation involving semistructured interviews to explore the perception of COPD, expectations of interventions, and attitudes toward TCM, among other aspects (phase 2; 3 months); and (3) a cross-sectional DCE, which aims to understand participants’ preferences for the TCM interventions and assess the relative importance of different attributes of treatment scenarios through a questionnaire (phase 3; 4 months).

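### The Phase 3 rule takes the size of a raw mixed-logit coefficient as relative strength and its significance as meaning, so a ranking built on it could mislead, depending on unit and coding

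*Protocol article*

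**What the plan says.** In the protocol article, under Methods, Data Analysis, Phase 3:

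- Model: "The core analysis of the DCE data will used a mixed logit model".
- Regressors: the model is set up "with the choice outcome as the dependent variable and the attribute levels as independent variables".
- Unit of the coefficient: "The model estimates a regression coefficient (β) for each attribute".
- Interpretation: "where a significant β denotes a meaningful impact on preference, with its sign and magnitude indicating the direction and relative strength of influence, respectively".
- Heterogeneity: "The associated SD of β quantifies the heterogeneity in preferences for that attribute among participants".

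The outputs that depend on this are promised elsewhere. Study Design says the discrete choice experiment will "assess the relative importance of different attributes of treatment scenarios through a questionnaire". The Introduction names as part of the objective "the trade-offs for the factors of treatment scenario options, such as clinical effectiveness, cost, and side effects". Data Integration says the combined results will show which factors weigh most in treatment decisions and how this differs between subgroups.

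Attributes and levels are not yet chosen. Study Design leaves them to the literature review and the interviews, so units, ranges and coding are open.

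**The concern.** A logit coefficient is utility per unit of its regressor. Its size depends on how the regressor is scaled and, for level-coded attributes, on which level is the reference. The rule compares sizes across attributes without mentioning either, and cost is one of the factors the study names.

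The text is also unclear about what β is. If levels are coded, an attribute with three or more levels has several coefficients and no single magnitude. If there is one coefficient per attribute, a multi-level attribute must enter as a numeric term, and the unit problem then applies in full.

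Equating significance with a meaningful impact makes the label depend on the number of respondents. It also attaches the label to β, that is, to the mean. In a mixed logit, an attribute on which patients hold strong but opposite views can have a mean near zero.

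At stake is the attribute ranking, which is a main quantitative result and feeds the joint display with the interview themes.

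**Working it through.** The protocol gives no coefficient, level range or resulting sample size for the choice experiment in the text at hand, so there is no figure of its own to reproduce. The check is a simulation on assumed inputs, followed by hand arithmetic on its output.

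**Inputs.** From the protocol: two alternatives plus an exit option in each choice set. Assumed: 300 respondents, 10 choice sets each, efficacy with 2 levels, side effects with 3 levels, cost at 100, 300 and 500 yuan, and the same preferences for everyone. The model fitted was a conditional logit, which is enough to show the effect of unit and coding.

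**1. Unit of cost.** The same data were fitted three times with linear cost. The efficacy coefficient was 0.906 and that of the worst side-effect level was 0.840 in absolute value each time.

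| Cost unit | Absolute β for cost | Rank of cost by raw β | Log-likelihood |
|---|---|---|---|
| 1 yuan | 0.0029 | last | -2975.323 |
| 100 yuan | 0.290 | last | -2975.323 |
| 1,000 yuan | 2.904 | first | -2975.323 |

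**2. Utility range.** Range = best minus worst level utility. Share = range divided by the sum of ranges.

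- Cost: 0.2904 per 100 yuan × 4 = 1.162
- Efficacy: 0.906
- Side effects: 0.840
- Sum: 2.908

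The shares are about 39.9%, 31.2% and 28.9%, and they are the same in every cost unit.

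**3. Several levels.** With all attributes dummy-coded and 100 yuan as reference, cost had coefficients -0.532 (300 yuan) and -1.170 (500 yuan). The largest absolute coefficients were cost 1.170, efficacy 0.906 and side effects 0.841, which is the same order as in step 2. If 300 yuan is the reference instead, the cost coefficients become +0.532 and -1.170 + 0.532 = -0.638. The largest is now 0.638, and cost falls to last. The range is unchanged: 0.532 + 0.638 = 1.170.

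**4. Significance.** Smallest efficacy coefficient with two-sided p < 0.05, as 1.96 × SE:

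| Respondents | SE | 1.96 × SE |
|---|---|---|
| 75 | 0.124 | 0.243 |
| 150 | 0.087 | 0.170 |
| 300 | 0.062 | 0.122 |
| 1,200 | 0.031 | 0.061 |

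An estimate of 0.10 would fall short with 300 respondents (0.10 < 0.122) and pass with 1,200 (0.10 > 0.061).

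**5. Opposed preferences.** Assume a normal random coefficient with mean 0 and SD 1.0. Then P(|β| > 0.5) = 0.617, so about 62% of patients have a coefficient of at least moderate size although the mean is zero.

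**6. Trade-off.** Efficacy coefficient divided by the absolute cost coefficient = 0.906 / 0.2904 × 100 = 312 yuan, in every cost unit.

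**The case against.** The strongest defence is that the text is compatible with level coding. Attribute levels are named as the regressors, nothing says cost will be linear, and coefficients within one logit model share a scale, so level contrasts can be compared in size. Step 3 bears this out when the reference is an end level. This stands, and it limits the consequence to something that could happen. It does not rescue the rule, which names neither coding nor reference level and then speaks of a single coefficient per attribute.

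Three stronger readings are tempting, and the documents do not support them.

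- *That the ranking would be wrong.* This needs a numeric term or an unlucky reference level. The protocol commits to neither.
- *That the trade-offs would be wrong.* Trade-offs are ratios of coefficients from the same model, and the rule does not distort them (step 6). No calculation is named, but an article may leave that to the full plan.
- *That an attribute with a non-significant mean would be declared unimportant.* The text does not state that converse, and it does interpret the SD: "The associated SD of β quantifies the heterogeneity in preferences for that attribute among participants". What is missing is only that mean and SD be read together when an attribute is judged.

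It can also be said that utility range depends on the levels the designers choose. That is true. With cost shown only from 100 to 300 yuan, the linear fit gives a range of 0.2904 × 2 = 0.581 and a share of 0.581 / (0.581 + 0.906 + 0.840) = 25.0%, which puts cost last. Range-based importance must therefore be reported as conditional on the levels shown.

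**Conclusion.** The point holds as a wrongly stated interpretation rule, not as missing detail. The article says how magnitude and significance are to be read, gives no condition, and offers no other route to the relative importance it promises. Under a numeric cost term the ranking can change from last to first with the unit alone. Under level coding it can change with the reference level. The significance label moves with sample size under any coding.

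The figures rest on assumed attributes, levels, preferences and sample sizes, and on a conditional logit. They show that the rule can fail and how, not how far this study's results would be off. The design and the fitted model are not affected, and the article reports the choice experiment as still in progress, so the rule can be corrected before analysis.

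**What to change.** Revise the Phase 3 paragraph as follows.

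1. Reconcile the coefficient per attribute with levels as regressors: estimate level-specific coefficients, or state for each attribute how it is coded, with unit and reference level.
2. Rank attributes by utility range (best minus worst level) as a share of the sum of ranges, with confidence intervals, and say that this is conditional on the level ranges shown. Comparing named level contrasts would also be defensible.
3. Replace the equation of significance with meaningful impact by effect size and confidence interval.
4. State that the mean and SD of β are read together, so that an attribute with opposed preferences is not judged on its mean alone.

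As a suggestion only, since the text contains no error here: report trade-offs as coefficient ratios with intervals.

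The cost is a few sentences in the plan and post-estimation commands on the same model. No new data are needed.

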#### Data Integration

For the analysis and interpretation of the 2 datasets, a joint display approach will be used to visually integrate and present the mixed methods findings [39]. After all data have been collected, the quantitative results will be mapped onto the qualitative themes to examine both the similarities and divergences between patients’ reported experiences and their expressed preferences in hypothetical treatment scenarios. This joint display of qualitative and quantitative findings will facilitate a holistic interpretation, highlighting which factors most strongly influence treatment decisions and how these preferences vary across patient subgroups. The final presentation will include integrated tables and figures illustrating the convergence and complementarity of the quantitative and qualitative data.

### Ethical Considerations

This study was reviewed and determined to be exempt from full ethical review by the ethics committee of Guangdong Provincial Hospital of Traditional Chinese Medicine on November 6, 2023 (ZM2023-405). Informed consent will be obtained from all participants.

## Results

On the basis of the search strategy we formulated (Multimedia Appendix 1), a total of 18,188 articles published after 2016 were initially identified in the English- and Chinese-language databases. The outline of the semistructured interview guide for this study has been developed (Table 1). Further clinical evidence updates, qualitative interviews, and DCEs are still ongoing and will be completed by April 2026.

## Discussion

### Expected Findings

In this study, we seek to understand the treatment preferences and needs of patients with COPD regarding TCM. Our findings are anticipated to provide new insights into how patients’ personal values and experiences shape treatment choices, helping physicians tailor clinical decisions to individual characteristics and needs.

EBM is defined as “the conscientious, explicit, and judicious use of the current best evidence to make medical decisions for individual patients” [40]. True EBM prioritizes individualized patient care by integrating clinical evidence with the unique contexts, experiences, and preferences of patients [41]. However, over the years, investigators have been committed to addressing patient population and subgroup-specific issues when designing and conducting clinical studies, often at the expense of individual patient differences to achieve more generalized findings and broader application prospects. Nevertheless, contemporary research, guideline development, and even clinical decision-making continue to insufficiently reflect individual patients’ values and preferences [42,43].

The personal experience of patients is extremely important and difficult to standardize, and conclusions drawn from studies on general patient populations should not outweigh those drawn by individual patients through their own experiences. Therefore, recent advances in EBM call for a more balanced approach that integrates critical evidence appraisal with patients’ values and preferences through SDM [44]. Achieving this integration requires clinicians to invest substantial time and effort in explaining, discussing, and negotiating treatment options with patients.

Previous studies on the treatment preferences of patients with COPD have mainly focused on conventional therapies such as inhalers, pharmacotherapy, and lung transplantation [45,46]. A pilot study by our team suggested that preferences for TCM may be influenced by perceived efficacy, side effects, and cost, but these findings require validation in larger samples [29]. Moreover, previous research has rarely examined patient perceptions of specific TCM interventions or accounted for individual values, experiences, and cultural factors.

This study has several strengths. First, it comprehensively captures the preferences and needs of patients with COPD regarding TCM through an exploratory sequential mixed methods study design that allows for a comparative analysis examining the relationship between patient preferences and individual backgrounds, helping identify patterns of homogeneity or divergence in treatment inclinations. Second, the use of narrative medicine in the interviews enables a deeper exploration of patients’ true experiences and perceptions, mitigating biases that arise when patients favor previously used treatments even when there is new evidence suggesting alternatives [47]. Finally, including patients from diverse hospital backgrounds and with diverse treatment experiences ensures that multiple perspectives are represented.

However, several limitations should be acknowledged. Patient preferences may still be influenced by cognitive perceptions, social determinants, environmental factors, or previous experiences, which could limit generalizability. Future multicenter studies with larger samples are needed to validate and extend these findings.

### Dissemination

The findings will be shared at national and international conferences focused on respiratory and integrative medicine. For scientific publication, results will be submitted to peer-reviewed journals related to respiratory care, patient-centered medicine, or integrative medicine. To reach patients and caregivers, summaries will be disseminated via patient organizations, hospital newsletters, and social media channels. These efforts aim to ensure that the study results are accessible and understandable to both the scientific community and the wider public.

### Conclusions

In conclusion, this exploratory sequential mixed methods study will generate empirical evidence on the treatment preferences of patients with COPD regarding TCM, offering a foundation for SDM and patient-centered COPD care. The anticipated findings will contribute to personalized treatment strategies; inform integrative guideline development; support SDM; and, ultimately, improve patient adherence and satisfaction. Future work will extend recruitment across multiple regions and countries to enhance generalizability and explore digital health applications that integrate patient preference modeling into clinical decision support systems.

## Data Availability

Data sharing is not applicable to this article as no datasets were generated or analyzed during this study. However, collective data from future studies will be made available as supplementary files alongside the manuscript.

## Appendix

Multimedia Appendix 1 Detailed search strategy.

## Abbreviations

TCM: traditional Chinese medicine
COPD: chronic obstructive pulmonary disease
DCE: discrete choice experiment
EBM: evidence-based medicine
PRISMA: Preferred Reporting Items for Systematic Reviews and Meta-Analyses
SDM: shared decision-making
